### Implementation

Understanding the urgent need to enhance MH outcomes in Assam, the Population Council Consulting Pvt. Ltd. (PCC), in collaboration with partners like Nivi Inc., Sitaram Bhartia Institute of Science and Research (SBISR), the Federation of Obstetric and Gynecological Societies of India, and the Centre for Northeast Studies and Policy Research, has launched the e-SAATHI initiative. This program aims to pilot and expand a chat-based digital support system for MH, designed to increase access to vital health information and strengthen maternal and newborn health across 10 districts in Assam through a comprehensive, multifaceted strategy.

e-SAATHI forms partnerships around a successful digital platform that empowers women to make informed choices about their reproductive health, promotes self-care, and connects users to reliable MH information and services throughout pregnancy and after childbirth. Given the obstacles pregnant women encounter in Assam, our approach is designed to both enhance and work alongside current public health programs related to MH. Most important, this solution helps reduce delays in seeking care by supporting women along their entire MH journey [24]. By maintaining engagement with expectant mothers from pregnancy through the postnatal period, the chat-based platform can help build greater awareness around healthy pregnancies (through timely and gestationally appropriate messages), encourage self-care practices, reinforce the value of ANC, facility-based births, and postnatal follow-up. It also facilitates timely connections with quality MH service providers, ensuring women get the safe and respectful care they need during this important period.

### Chatbot

A key component of the e-SAATHI project is the chatbot messaging on MH information. It consists of a set of weekly tips and periodic reminders/check-ins that we send to subscribed users from prenatal week 10 through postnatal week 15. Women can subscribe to the free program in 1 of 2 ways: (1) clicking on a social media advertisement; or (2) scanning a QR code while visiting a health facility (public or private) that has engaged with the project. Both actions launch an automated conversation in WhatsApp that prompts the woman to onboard to the askNivi chatbot (accept terms and conditions and provide basic demographic information) and then subscribe to the ANC/PNC program (initially provide expected due date and preferred provider). Women who scan a QR code at a facility have the option of getting 1-on-1 support from a provider—typically a nurse—trained in user onboarding. The messages will be developed in alignment with the National Health Mission and WHO, ANC, and PNC guidelines (Figure 1).

**Figure 1. F1:**
[figure not shown]
Proposed digital chat-based pathway for maternal health. ANC: antenatal care; EDD: expected date of delivery; LMP: last menstrual period; PNC: postnatal care; WHO: World Health Organization.

The intervention will be implemented over 3 distinct phases: (1) establish and operationalize MH chatbot (0‐3 mo); (2) engagement, monitoring, and iterative improvement (4‐24 mo); and (3) scale-up (25‐36 mo).

### Phase 1: Establish and Operationalize MH Chatbot (January 2023-March 2023)

The MH chatbot will be developed in partnership with gynecologists, adhering to ANC and PNC guidelines established by the WHO and the National Health Mission. To ensure that all content aligns with current evidence and clinical standards, a diverse panel of health professionals will be convened. Additionally, a Women’s Ambassador Forum, comprising local community members—including pregnant and recently delivered women—will be formed to review the chatbot’s content for clarity, contextual relevance, and completeness. Upon completion of development, pilot testing will be conducted with a select group of approximately 15‐20 pregnant and postpartum women, including members of the Women’s Ambassador Forum, to assess message comprehension, cultural appropriateness, and usability. Feedback from users and subject matter experts will continually inform ongoing refinements to message wording, sequencing, and delivery as content is periodically updated.

We will collaborate with health care providers in both private and public hospitals to facilitate the enrollment of pregnant and postnatal women onto the digital system via the WhatsApp chatbot. Once enrolled, participants will receive 2 to 3 tailored messages per week, providing guidance aligned with their stage of gestation or weeks postnatal—including reminders for visits to designated MH providers—and offering opportunities to request additional support or submit feedback regarding their care. Additionally, this solution enhances MH provider workflows by using the MH digital support system. It streamlines onboarding processes, delivers automated reminders and follow-up prompts for both users and providers, and implements structured feedback mechanisms for ongoing improvement. These features collectively improve operational efficiency, enable prompt engagement, and ensure user feedback is systematically integrated into service delivery.

### Phase 2: Engagement, Monitoring, and Iterative Improvement (April 2023-September 2025)

#### Engagement

Onboarded women will be regularly engaged by health care providers or the research team whenever visiting the health facility to identify any challenges they face while using the chatbot. Additionally, feedback will be collected from users regarding the quality and usefulness of the services provided by the e-SAATHI chatbot.

#### Monitoring and Iterative Improvement

The monitoring and evaluation process will be conducted on users and health care providers. This study uses a mixed method, pre-post implementation design to evaluate the introduction and scale-up of the e-SAATHI MH chatbot in Assam. While this design enables comprehensive assessment of both quantitative outcomes and qualitative experiences, we acknowledge that the absence of randomization limits the strength of causal inference. To address potential sources of bias, we will implement several strategies, including adjustment for district-level clustering, accounting for secular trends over time, and controlling for measured confounders in the analysis. These approaches aim to strengthen the validity of our findings and provide a nuanced understanding of the intervention’s impact in real-world settings.

All the developed data collection instruments and procedures will be pretested in settings like those in which they will be administered. Guidance will be sought from postnatal women who have recently given birth when finalizing the instruments to ensure that questions and the data collection procedures are conducted with appropriate sensitivity and are not perceived as stigmatizing. The study tools will be pretested among a small group of women with characteristics similar to those of the study population to identify potential negative consequences and will be modified accordingly. Study tools for postnatal women will be translated and pretested in Assamese and Hindi.

The study comprises 5 main data collection tools that are described in Table 1: (1) in-depth qualitative interviews with MH providers; (2) in-depth qualitative interviews with postnatal women; (3) telephone interviews with postnatal women and MH chatbot users; (4) health facility inventory; and (5) MH digital platform program data.

**Table 1. T1:** Data collection activities.^a^

	1. IDIs^b^ with health care providers	2. IDIs with postnatal (PN^c^) women	3. Survey with PN women	4. Facility inventory and routine data	5. MH^d^ data from chatbot platform
Study population	Purposively selected providers from various care levels (public and private)	Purposively sampled PN women using chatbot <6 mo since childbirth	PN women recently given birth in last 2‐8 wk	Facility providing MH services	Pregnant and PN women onboarded to chatbot (deidentified)
Sample size	10 from range of facility levels periodically	2‐4 women per facility—periodically	200 PN women	Each facility taking part in the project	All women who use chatbot
Location of activity	Private room at health facility or mutually agreed site	Private room at health facility or mutually agreed site	Recruitment at PNC^e^ ward then short interview (2‐8 wk later)	Facility level data (deidentified)	Online program data
Timing	Baseline and periodically 6‐9 mo	Baseline, midline, and endline	Baseline, then periodically (9 mo after chatbot introduction)	Quarterly	From initiation of chatbot to end of project
Method	In-depth face-to-face interview by researcher	In-depth face-to-face interview by researcher	Short in-person/telephone survey by researcher	Facilities visited by researcher	Analysis of chatbot program data

a Analysis of baseline, midline, and endline data will occur after the completion of each respective phase; interim analyses will be performed after midline (2026) and final analyses after endline (2027).

b IDI: in-depth interview.

c PN: postnatal.

d MH: maternal health.

e PNC: postnatal care.

First, this includes any MH provider (at least 10) over 18 years, who consent to be interviewed and work in one of the public or private facilities in the study areas, nurses, midwives, auxiliary nurse midwives, Accredited Social Health Activists (ASHAs), and doctors at health facilities engaged in the digital MH support system. The purpose of the interviews with MH providers is to identify facility and provider-specific issues that may affect the delivery of care and uptake of women onboarding onto the chatbot. Researchers will use a short in-depth interview (IDI) guide to ask respondents about their expectations regarding the MH chatbot, its strengths and weaknesses, develop an in-depth understanding of the process of introducing the chatbot, and how it might be improved and subsequently scaled up. Data will be analyzed iteratively after each collection wave to inform ongoing implementation and comprehensively the completion of phase 2.

Second, this will be conducted with a subsample of women (n=10) who used the MH chatbot and accessed its services in a facility. These interviews will be used to gain a deeper understanding of the motivations, perceptions, and priorities of women using the chatbot and facility services. Researchers will use a short IDI guide to ask respondents on their experience of using the MH chatbot, its strengths and weaknesses, and how it might be improved. Women will be at least 18 years old, have consented to the interview, and have given birth in a facility within the preceding 6 months. Data will be analyzed iteratively after each collection wave to inform ongoing implementation and the comprehensive completion of phase 2.

Third, postnatal women who have given birth and have experienced MH journey and/or used *askNivi* chatbot (>18 y age) will be approached in a postnatal ward at a facility. Women who consent to participate will be contacted telephonically between 2 to 8 weeks after the date of delivery for a telephonic or in-person survey. The study team will note their identifying information for future contact separately from the data. During the recruitment or enrollment at the facility, the research assistant will ask permission to contact the woman. A member of the study team will call and agree on a time that suits them. That same member of the team will then call to interview at the conveniently decided time. The short dipstick survey will cover the quality of care, experiences during pregnancy (number of ANC contacts, etc), childbirth and postnatally, and experience of using askNivi chatbot. Women who had loss or severe complications during childbirth were excluded. We will use the dipstick survey parameters field feedback to modify/adapt the composite quality score of maternal and newborn care as a composite measure designed to assess the quality of maternal and newborn health services received [24]. Each indicator will be scored based on whether the recommended standard will be met, typically using a binary (yes/no) scale. The scores for all indicators will then be summed to produce a total score, which will often be standardized to a percentage for ease of interpretation. This approach will allow for comparison of service quality across facilities and overtime and will help identify specific areas for improvement [24]. Quantitative analyses will be conducted after baseline, midline, and endline data collection points. Data cleaning and quality checks will occur fortnightly during collection with a comprehensive pass before midline and endline analyses.

Fourth, a short checklist including facility staffing levels; maternity unit capacity, medicines, supplies, and infrastructure; educational materials, job aids and protocols; health management information system and information and communication technology; facilitation and management of emergency referrals and transport; and other MH interventions available in the facility. This checklist will be administered to the in-charge or delegate of the facility. Statistics related to routine program data on utilization or uptake of maternal and newborn health services (ANC, PNC, births, and deaths) will be collected. Monthly trends in the numbers of new and continuing ANC and PNC clients will be obtained from facility records.

Fifth, this includes responses from women who have joined the MH chatbot (e-SAATHI), including demographic information and use of services. The data used is from all women who interact with the MH platform. Women who are on board with the chatbot permit their data to be used (deidentified).

The study uses a mixed methods approach to comprehensively document and monitor the rollout of the mental health chatbot for pregnant and postnatal women in Assam. Implementation is guided by continuous field feedback, data on onboarding and user engagement with the chatbot, the effectiveness of online campaigns, and qualitative and quantitative impact assessments. By adopting a participatory CLA methodology, the program integrates women’s perspectives and feedback from the earliest proof of concept, beginning in 5 facilities and then expanding across 3 districts to ultimately reach 10 districts within 3 years. These iterative CLA cycles, paired with regular evaluations of operational and financial sustainability, foster a deeper understanding of implementation challenges, including acceptability and feasibility. Upon completion of phase 2, a detailed impact evaluation will assess the effectiveness of the intervention, ensuring that crucial insights and real-world evidence are retained throughout the study’s progression. User engagement with the chatbot will be tracked as an automatically generated metric, supporting ongoing learning and adaptation to enhance the system. For the qualitative interviews and dipstick surveys, which are single, one-time interactions, with no follow-up assessments. However, we will systematically record and report the number of individuals who refuse participation or cannot be contacted at recruitment, along with reasons for refusal when volunteered. For the chatbot, we will also report the number of users who disengage before completing the interaction.

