#### Quantitative Analysis

Raw quantitative data collected from the postnatal women’s survey (dipstick survey) will be cleaned and checked for errors and outliers. Data cleaning and quality checks will occur fortnightly during collection with a comprehensive pass before midline and endline analyses. Descriptive statistics (means, SDs, medians, and frequencies) will summarize baseline characteristics and outcomes. The primary outcome, the composite quality score of maternal and newborn care [24] and secondary outcomes (service uptake indicators, user-reported knowledge and self-care practices, and satisfaction with care) will be compared between baseline and follow-up.

Normality will be tested (Shapiro-Wilk). Parametric (*t* tests, ANOVA) or nonparametric (Wilcoxon and Mann-Whitney) tests will be used as appropriate. Categorical variables will be analyzed using chi-square or Fisher exact test. Multivariable analyses will use generalized linear/logistic mixed models to adjust for clustering (facility/district) and confounders (age, parity, socioeconomic status, dose of exposure-engagement frequency, and enrollment channel). For repeated measures, mixed-effects models will assess changes over time. Multiple comparisons will be adjusted using Bonferroni or FDR. All analyses will be performed in IBM SPSS Statistics (Version 29.0; IBM Corp) and R Core Team. Results will be visualized with tables and graphs. Statistical significance is set at *P*<.05, with effect sizes and 95% CIs reported.

Interim analyses will be conducted after midline data (Phase 2) collection completion in 2026; final analyses will be performed after endline data collection in 2027.

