## Results

The e-SAATHI study was formally funded in September 2022, marking the commencement of project activities. Since the initiation of the program, significant progress has been achieved in both the onboarding of health care facilities and participant recruitment. As of December 2025, a total of 210 health facilities across Assam have been successfully integrated into the e-SAATHI network. A total of 201,813 women have been enrolled to receive MH support through the chatbot platform.

Chatbot-based data collection was launched in April 2023 and is scheduled to continue through June 2027, ensuring comprehensive coverage of the intervention period. The collection of qualitative and quantitative evaluation data began in November 2023, providing a robust foundation for assessing both user experiences and measurable outcomes.

Interim analyses are planned following the completion of midline data collection in 2026, which will offer early insights into the effectiveness and operational feasibility of the intervention. Final analyses are scheduled to take place after endline data collection in 2027, at which point the full impact of the e-SAATHI program will be evaluated and published. The primary outcome of interest is the change in the composite quality score of maternal and newborn care, serving as a key indicator of the intervention’s effectiveness. Secondary outcomes include a range of service uptake indicators, user-reported knowledge and self-care practices, and satisfaction with care received. The study will also assess operational feasibility, including the integration of providers into the digital system and the identification of barriers such as digital literacy and connectivity challenges.

As of the writing of this paper (December 2025), we are completing phase 2 and initiating in-depth impact evaluation.

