## Discussion

### e-SAATHI’s Implications

The introduction of the e-SAATHI intervention represents a significant advance in the realm of MH care, particularly within low-resource settings such as Assam, India. Assam has the highest maternal mortality ratio in India at 195 per 100,000 live births, nearly double the national average [1]. Given this context, there exists an urgent need for innovative solutions to address systemic gaps and improve MH outcomes. mHealth interventions, including chatbots and digital communication platforms, have demonstrated promise in improving MH care use in LMICs [26]. The implementation of e-SAATHI aligns with these global priorities, offering tailored health information, decision-making support, and continuous engagement to pregnant and postpartum women through digital channels. The observed changes in the composite quality score of maternal and newborn care [24] and domains will provide robust evidence of improvements in the quality and comprehensiveness of MH services. Secondary outcomes, including increased service uptake and improved knowledge/self-care, will further support the effectiveness and scalability of the intervention.

The e-SAATHI protocol leverages global evidence on the efficacy of mHealth tools in promoting maternal care use. Meta-analyses have consistently highlighted that digital health interventions such as chatbots and mobile messaging platforms significantly enhance key MH metrics, including ANC visits and facility-based delivery rates [26]. As a chatbot-driven initiative, e-SAATHI addresses longstanding gaps in MH education and accessibility, particularly in underserved regions. By providing stage-specific health information tailored to users’ gestation periods, the intervention reinforces global efforts aimed at improving maternal knowledge, autonomy, and continuity of care [27].

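### The article promises to account for secular trends, but its stated analysis has no trend term separate from the pre-post contrast

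*Protocol article*

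**What the plan says.** The design is stated in Monitoring and Iterative Improvement: "This study uses a mixed method, pre-post implementation design to evaluate the introduction and scale-up of the e-SAATHI MH chatbot in Assam". The same paragraph concedes that the lack of randomization weakens causal inference, and offers three remedies: "adjustment for district-level clustering, accounting for secular trends over time, and controlling for measured confounders in the analysis".

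Quantitative Analysis then describes the analysis. The primary composite quality score and the secondary outcomes "will be compared between baseline and follow-up". For adjustment, "Multivariable analyses will use generalized linear/logistic mixed models to adjust for clustering (facility/district) and confounders"; the five covariates are age, parity, socioeconomic status, how often the woman engaged with the chatbot, and how she enrolled. One further sentence gives mixed-effects models for change over time, limited to repeated measures. The section opens on the dipstick survey and names no other quantitative source.

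Three other places matter:

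- Later in Monitoring and Iterative Improvement, the interviews and dipstick surveys are described as one-off contacts without follow-up.
- For the facility tool, "Monthly trends in the numbers of new and continuing ANC and PNC clients will be obtained from facility records".
- In e-SAATHI’s Implications, the observed changes in the composite score "will provide robust evidence of improvements in the quality and comprehensiveness of MH services".

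**The concern.** Two of the three promised remedies, clustering and measured confounders, reappear in the analysis section. The third, secular trend, does not. That is a mismatch between two statements in one article, and it concerns the main threat to an uncontrolled before-and-after comparison.

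Any improvement in maternal care in Assam that would have happened anyway enters the baseline versus follow-up difference in full. None of the listed covariates stands in for calendar time. Engagement frequency and enrolment channel are aspects of exposure to the chatbot. If the analysis is run as written, background drift is counted in the estimated change, while the article tells its reader that drift has been dealt with.

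**Working it through.** The article gives no power calculation, effect size or SD, so there is no stated figure to reproduce. The checks are whether trend and intervention can be separated, how much drift could matter, and whether the remedy can work.

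**1. Can the stated contrast separate trend from intervention?** Take wave means as the data and suppose all sites start together. Count the columns of the model and its rank.

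| Waves | Model | Columns | Rank | Result |
|---|---|---|---|---|
| 2 | intercept + post + time | 3 | 2 | not separable |
| 3 | intercept + post + wave as category | 4 | 3 | not separable |
| 3 | intercept + post + linear time | 3 | 3 | separable, 0 residual df |

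In the second row, the post indicator is the sum of the two later wave indicators. In the third row, with equally spaced waves y1 (before), y2 and y3 (after), the slope is y3 − y2 and the effect is (y2 − y1) − (y3 − y2) = 2·y2 − y1 − y3. Linearity cannot be checked, because no degrees of freedom remain. The estimate is also less precise: its variance is (4 + 1 + 1)σ²/n = 6σ²/n, against 2σ²/n for y2 − y1, so the SE is √3 ≈ 1.73 times as large.

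**2. Does the change-over-time model help?** At the level of the woman it has nothing to work on, since each is interviewed once. At facility level its time variable would be the survey wave, which is the pre-post contrast again.

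**3. How often would drift alone give P<.05?** Inputs are two-sided alpha 0.05 (the article gives P<.05; two-sided is assumed), zero intervention effect, and clustering ignored. Table 1 gives 200 postnatal women without saying whether that is per wave or in total, so both 200 and 100 per wave are shown. The drift sizes are assumptions.

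For drift d in SD units, SE = √(2/n) and the rejection rate ≈ Φ(d/SE − 1.96). At n = 200, SE = √(2/200) = 0.10. For d = 0.2 this is Φ(2.00 − 1.96) = Φ(0.04) ≈ 52%.

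| Drift in score | 200 per wave | 100 per wave |
|---|---|---|
| 0.1 SD | 17% | 11% |
| 0.2 SD | 52% | 29% |
| 0.3 SD | 85% | 56% |

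A binary indicator behaves similarly. The Introduction says about half of women receive four or more ANC visits. From 50%, drifts of 5, 10 and 15 percentage points give 17%, 52% and 86% at 200 per wave, and 11%, 29% and 57% at 100.

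**4. Can staggered onboarding separate them?** The Population section has 5 facilities first, then 3 districts, then 10. As an illustration, take three onboarding groups starting at different waves, with group effects, wave effects and an intervention indicator. The rank is 6 of 6 columns with three waves and 7 of 7 with four. Separation is then possible, provided the groups are observed across several waves. Monthly facility counts could meet that condition if they cover months before onboarding. For the survey, the article does not say.

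**The case against.** The strongest defence is that this is a condensed article: model terms are commonly left to an analysis plan that is not shown, the trend adjustment is promised, and the limitation is disclosed twice, in Monitoring and Iterative Improvement and in Limitations. Silence about a detail would indeed be no finding. Here, however, the article sets out the analysis and carries through two of its three promises. The caveat in Limitations likewise mentions only efforts on confounders and clustering. The mismatch stands.

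The objection does defeat several stronger readings that a reader might infer:

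- *There is no time term at all.* There is a change-over-time model; it does not fit one-time surveys.
- *Time and intervention are the same variable throughout.* That is exact only with a common start and two or categorical waves. Entry is staggered, Table 1 ties survey timing to chatbot introduction, and surveyed women may or may not have used the chatbot, so exposure may vary within a wave. The user contrast is self-selected, as Limitations accepts, but it is not identical to time.
- *The monthly records could rescue the primary outcome.* They count ANC and PNC clients. The composite score comes from the survey.
- *The records and staggered rollout will go unused.* The article states no analysis for them; a fuller plan might.
- *All background improvement will be reported as a chatbot effect.* The disclosed limitation makes that too certain.
- *Midline interviews could be moved to facilities not yet onboarded.* Results says "a total of 210 health facilities across Assam have been successfully integrated", against 300 planned, which suggests up to 90 remain. But 200 women over 300 facilities is 200/300 ≈ 0.67 per facility, nothing shows these facilities have baseline interviews, women can enrol through social media without a facility, and scale-up from October 2025 may bring them in before the 2026 midline. The documents do not support that redesign.

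**Conclusion.** The concern holds in limited form. The article says its analysis accounts for secular trends, and the analysis it specifies does not show how. As written, the primary pre-post change would include background drift. Where sites share a start, no covariate in the stated model can remove it, and a linear trend over three waves would rest wholly on assumed linearity.

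The size is illustrative: about 52% of studies would reach P<.05 from a 0.2 SD drift with no effect at 200 women per wave, and about 29% at 100. Drift and wave size are assumptions, and a shorter gap between waves or an allowance for clustering would lower the rates. The figures show that modest drift matters; they do not predict this study's result.

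**What to change.** 1. **Service uptake.** Analyse the monthly facility ANC and PNC counts already being collected with a segmented or staggered-start model. Use each facility's onboarding month as the start of exposure, with calendar-month and facility effects.
2. **Composite quality score.** If the survey covers groups onboarded at different times, add calendar-period effects and district or onboarding-group effects, using site onboarding dates. If it does not, state that the primary pre-post change cannot be separated from secular trend, remove the secular-trend claim for that outcome from Monitoring and Iterative Improvement, and soften the sentence on robust evidence in e-SAATHI’s Implications.

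The cost is some extra analysis work and, where needed, a wording change; no additional women are required. The drawbacks should be stated too. Rollout order is not random, so early and late facilities may differ in their trends. Social-media enrolment exposes women attending facilities not yet onboarded, which biases the staggered comparison toward no effect.
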